## Abstract

**Background:**

Surviving breast cancer does not necessarily mean complete recovery to a premorbid state of health. Among the multiple psychological and somatic symptoms that reduce the quality of life of breast cancer survivors, persistent pain after breast cancer treatment (PPBCT) with a prevalence of 15–65% is probably the most invalidating. Once chronic, PPBCT is difficult to treat and requires an individualized multidisciplinary approach. In the past decades, several somatic and psychological risk factors for PPBCT have been identified. Studies aiming to prevent PPBCT by reducing perioperative pain intensity have not yet shown a significant reduction of PPBCT prevalence. Only few studies have been performed to modify psychological distress around breast cancer surgery. The AMAZONE study aims to investigate the effect of online cognitive behavioral therapy (e-CBT) on the prevalence of PPBCT.

**Methods:**

The AMAZONE study is a multicenter randomized controlled trial, with an additional control arm. Patients (*n*=138) scheduled for unilateral breast cancer surgery scoring high for surgical or cancer-related fears, general anxiety or pain catastrophizing are randomized to receive either five sessions of e-CBT or online education consisting of information about surgery and a healthy lifestyle (EDU). The first session is scheduled before surgery. In addition to the online sessions, patients have three online appointments with a psychotherapist. Patients with low anxiety or catastrophizing scores (*n*=322) receive treatment as usual (TAU, additional control arm).

Primary endpoint is PPBCT prevalence 6 months after surgery.

Secondary endpoints are PPBCT intensity, the intensity of acute postoperative pain during the first week after surgery, cessation of postoperative opioid use, PPBCT prevalence at 12 months, pain interference, the sensitivity of the nociceptive and non-nociceptive somatosensory system as measured by quantitative sensory testing (QST), the efficiency of endogenous pain modulation assessed by conditioned pain modulation (CPM) and quality of life, anxiety, depression, catastrophizing, and fear of recurrence until 12 months post-surgery.

**Discussion:**

With perioperative e-CBT targeting preoperative anxiety and pain catastrophizing, we expect to reduce the prevalence and intensity of PPBCT. By means of QST and CPM, we aim to unravel underlying pathophysiological mechanisms. The online application facilitates accessibility and feasibility in a for breast cancer patients emotionally and physically burdened time period.

**Trial registration:**

NTR NL9132, registered December 16 2020.

## Administrative information

Note: the numbers in curly brackets in this protocol refer to SPIRIT checklist item numbers. The order of the items has been modified to group similar items (see http://www.equator-network.org/reporting-guidelines/spirit-2013-statement-defining-standard-protocol-items-for-clinical-trials/).

## Introduction

### Background and rationale {6a}

Persistent pain after breast cancer treatment (PPBCT) is highly prevalent [1]. In the acute phase following surgery, reconstructive surgery, radiotherapy, and chemotherapy, up to 50% of the patients suffer from pain [2, 3]. In around 30% (15–65%) of patients, this pain persists for 1 year or longer. Previously, it was thought that pain after mastectomy was mainly neuropathic, caused by damage to the intercostal brachial nerve (ICBN). However, pain may also originate from other sources such as lymphedema, scarring of tissues of the chest wall [4], or from muscle guarding [5]. Once chronic, PPBCT and secondary problems are difficult to treat and require a complex individualized multidisciplinary approach [6, 7]. The standard pharmacological treatment of PPBCT consists of antidepressants [8, 9], and capsaicin [10], but even though effective, intolerable side effects often limit (long-term) treatment. Interventional treatment options of PPBCT target the thoracic dorsal root ganglia, intercostal nerves [11], stellate ganglion [12], thoracic sympathetic chain [13], and fascia of the thoracic wall [14].

In the past decade, research has identified treatment- and patient-related factors increasing the risk for PPBCT. Treatment-related risk factors such as axillary lymph node dissection, radiotherapy, and intercosto-brachial nerve handling may directly increase tissue damage. Patient-related risk factors such as genetic haplotypes, young age, high BMI, pre-existing pain, high postoperative pain intensity, and psychological distress suggest a greater vulnerability of the nociceptive system that is prone to sensitization [15–18]. Quantitative sensory testing (QST) demonstrated the presence of central sensitization in patients with PPBCT [19–22]. Moreover, there is accumulating evidence that patients with persistent postsurgical pain have less efficient inhibitory modulation of afferent nociceptive signals [23–26].

Many interventions aiming at a reduction of nociceptive input and concomitant sensitization of the central nociceptive system have been studied, e.g., reducing the extent of surgery, aggressively treating perioperative pain and minimizing the radiation dose and field [2, 27]. So far, only perioperative ketamine and lidocaine have been found to significantly reduce chronic pain after various kinds of surgery [28]. Perioperative venlafaxine reduced the prevalence of PPBCT in one study [29]. The utility of paravertebral blocks during mastectomy in preventing long-term pain has been studied repeatedly with—despite good acute postoperative pain relief—no convincing preventive effect on PPBCT prevalence [30–36].

Anxiety and pain catastrophizing have emerged as the most robust psychological predictors of persisting postoperative pain [3, 15, 37, 38], including PPBCT [16]. Moreover, these psychological states have been shown to interfere with pain processing within the CNS [39–42]. Stress may alter the endogenous pain inhibition-facilitation balance, resulting in reduced net endogenous pain inhibition [43, 44]. Less endogenous pain inhibition increases the risk for central sensitization and leads to chronification of acute pain.

In contrast to most other identified risk factors for PPBCT, psychological variables are modifiable and can therefore be a target for intervention. Cognitive behavioral therapy (CBT) is the leading psychological treatment for chronic pain. It aims to reduce maladaptive cognitions and behaviors and replace these with more adaptive ones. Reducing anxiety and catastrophizing around the time of surgery may reduce prevalence of persistent pain [45, 46]. A recent meta-analysis showed that perioperative psychological interventions significantly reduced persistent pain and disability after different types of surgeries [47]. The search only identified two RCTs examining the effects on long-term pain after breast cancer surgery. Hadlandsmyth et al. found a 2-h postoperative psychological intervention to be feasible and acceptable, yet it did not significantly affect pain at three months [48]. A one-session preoperative internet-based intervention targeting pain catastrophizing before breast cancer surgery reduced the duration of postoperative of opioid consumption, yet no effect in pain intensity was found [49]. It should be noted that both studies used a single session intervention, which may not be sufficient to have a long-term impact on PPBCT. Moreover, neither study examined the effects beyond the 3-month period.

The AMAZONE study is the first to examine the long-term effects of a more intensive perioperative CBT program on the development of PPBCT in breast cancer surgery patients with high levels of anxiety and/or catastrophizing. Face-to-face CBT is challenging in the context of cancer treatment because of the demands it poses on patients, especially during treatment. Therefore, an online CBT (e-CBT) program was developed. e-CBT increases feasibility because it can be administered in the home environment and at a time that is convenient for patients. It has been demonstrated that (therapist-guided) e-CBT is as effective as face-to-face CBT [50]. A review supported feasibility and acceptability of internet-based interventions for breast cancer patients [51].

In addition to studying the effectiveness of the e-CBT intervention on reducing the prevalence of PPBCT, its effect on sensory (nociceptive) signal transmission and endogenous pain suppressing pathways is examined by means of quantitative sensory testing (QST) and conditioned pain modulation (CPM) to unravel potential underlying mechanisms.

### Objectives {7}

The primary objective is as follows: the primary aim of the project is to investigate the effect of online cognitive behavioral therapy (e-CBT) on the prevalence of PPBCT 6 months after breast cancer surgery in patients with high levels of preoperative anxiety or pain catastrophizing. The e-CBT intervention will be compared with an educational intervention consisting of information about surgery and a healthy lifestyle.

The secondary objective(s) is as follows: to examine the effects of e-CBT on nociceptive sensory signal transmission and central pain inhibiting mechanisms; to examine the effects of e-CBT on the intensity of acute postoperative pain in the week after surgery, cessation of postoperative opioid use, and on PPBCT prevalence after 12 months, PPBCT intensity and interference; and to evaluate the impact of e-CBT on anxiety, depression, catastrophizing, fear of cancer recurrence, and quality of life until 12 months post-surgery.

### Trial design {8}

This superiority trial is designed as a multi-center randomized controlled trial, with an additional non-randomized control arm. Breast cancer patients with high anxiety or catastrophizing levels will be allocated to either the e-CBT intervention or active control arm (EDU). Patients with low to normal levels of anxiety and catastrophizing will receive treatment as usual (TAU). The TAU group serves as an observational cohort and is followed parallel to the randomized trial (Fig. 1).

**Fig. 1 Fig1:**
[figure not shown]
Time schedule of enrolment. T0: 1–3 weeks pre-surgery, T1: postoperative week*, T2: 2 months follow-up, T3: 6 months follow-up, T4: 12 months follow-up. e-CBT, online cognitive behavioral therapy; EDU, online educational therapy; TAU, treatment as usual; QST, quantitative sensory testing; CPM, conditioned pain modulation

## Methods: participants, interventions, and outcomes

### Study setting {9}

Patients are recruited in several academic and specialized hospitals in the Netherlands all dedicated to the treatment of breast cancer.

### Eligibility criteria {10}

The eligibility criteria are as follows: women scheduled for primary breast cancer surgery with or without primary reconstructive surgery.

### Inclusion criteria all patients

Unilateral primary breast cancer surgeryAge ≥ 18 years old

### Inclusion criteria for the RCT (e-CBT&EDU)

Women scoring either ≥ 8 on the anxiety subscale of the Hospital Anxiety and Depression Scale (HADSa) [52], ≥ 3 on the Surgical fear item (i.e., “quite a bit” or “very much” [16];), ≥ 5 on the Concerns about Recurrence Scale (CARS) [53], or ≥ 18 on the Pain Catastrophizing Scale (PCS) [54]

### Inclusion criteria for the observational cohort (TAU)

Women scoring < 8 on the HADSa, < 3 on the Surgical fear item, < 5 on the CARS, and < 18 on the PCS

### Exclusion criteria all patients

Breast cancer surgery/treatment in the pastPreventive breast surgeryBilateral surgeryNot able to understand DutchNo internet accessVisual or hearing impairments interfering with reading and listening to the online materialKnown or suspected severe psychiatric disorderCurrent litigation procedure

### Who will take informed consent? {26a}

Patients are asked for participation by the local breast cancer teams, study nurses, and anesthesiologists involved in the perioperative breast cancer surgery procedure.

If patients are interested, they are offered verbal and written information followed by an appropriate reflection time of 48 h to 1 week, depending on the time-span between preoperative screening and surgery. In adaption to the COVID-19 pandemic, the informed consent procedure is also possible by telephone, video call, mail, and email.

### Additional consent provisions for collection and use of participant data and biological specimens {26b}

Separate informed consent is asked for the use of participant data for future research on breast cancer.

No biological specimens are taken.

## Interventions

### Explanation for the choice of comparators {6b}

To provide a control group with comparable intervention conditions to the e-CBT group, an online educational (sham) intervention is composed. Women randomized to this EDU group receive an intervention based on information about surgery, communication skills, and a healthy lifestyle. Content referring to psychosocial support is avoided. The number of online sessions and appointments with a therapist are equal to the e-CBT intervention.

Women with low to normal levels of anxiety and catastrophizing are allocated to the non-randomized control group receiving TAU. This group serves as reference group for the primary outcome PPCBT and for the QST/CPM measurements.

### Intervention description {11a}

#### AMAZONE e-CBT intervention

The AMAZONE e-CBT intervention is developed together with an experienced onco-psychologist and patient representatives of the Dutch Breast cancer Society and the MUMC+ patient panel. In addition, existing protocols for decreasing pre-operative anxiety and pain catastrophizing [48, 55–57] and fear of cancer recurrence (FCR) [58] were taken into account.

The intervention consists of education and skills training to better cope with pain after surgery and challenge and replace anxious and catastrophizing thoughts by more helpful cognitions. The key elements of the e-CBT are cognitive restructuring, relaxation exercises, coping with anxiety, activity-rest balance, and pleasant activity scheduling. As such, the intervention targets cognitive, emotional, behavioral, and physiological aspects of psychological distress.

The e-CBT intervention consists of five sessions, with one being delivered pre- and four post-operatively. Patients can follow the sessions at their own pace, but are recommended to follow the timeline as presented in Table 1. In addition to the five online sessions, three appointments with a therapist are scheduled. The appointments take place via video call (secured platform). The content is manualized and the duration is limited to 30 min. The purpose of the appointments is to monitor the intervention, increase motivation, and answer questions and concerns that occur during the intervention.

**Table 1 Tab1:** Summary of the e-CBT intervention

**1st appointment with the therapist:** introduction study intervention and e-CBT platform	
**Session 1: **1–2 weeks before surgery - Education: pain and factors contributing to pain experience; stress response - Relaxation exercises: progressive muscle relaxation, breathing exercises, visualization exercise	
**Day of surgery**	
**Session 2: **DoS + 7 days - Education: relationship between thoughts-feelings-bodily sensations-behavior; coping with anxiety; valued activities - Exercises: thoughts and activity diary	
**2nd appointment with the therapist:** introduction relaxation exercises and thoughts diary; discussion potentially hindering factors	
**Session 3: **DoS + 14 days - Education: different coping strategies; unhelpful and helpful thoughts - Exercises: cognitive restructuring	
**Session 4: **DoS + 21 days - Education: role of avoidance - Exercises: clarifying valued activities; SMART description of new valued activities	
**Session 5: **DoS + 28 days - Recap session 1-4 - Action plan: warning signs and helpful exercises and techniques	
**3rd appointment with the therapist:** discussion on helping thoughts, valuable activities, action plan; evaluation of most helpful elements of the program and how to continue	

*DoS* day of surgery, *SMART* Specific-Meaningful-Acceptable-Realistic-Time framed

Session 1 starts with discussing the reactions that can be expected when confronted with breast cancer and the upcoming surgery. The education part is devoted to pain, the different factors contributing to the pain experience, and the stress response. Relaxation techniques are introduced. Patients are asked to try out the different relaxation exercises (progressive muscle relaxation, breathing exercises and visualization exercise). As a recurring aspect of the intervention, patients choose one exercise and continue to practice this exercise on a daily basis.

Session 2 consists of three parts, the first being the relation between thoughts-feelings-bodily sensations-behavior. With the aid of a thoughts diary, patients learn to notice their own thoughts and reactions. Later in the intervention, this will serve to practice cognitive restructuring of the catastrophizing thoughts. The second part focuses on coping with anxiety and contains tips and exercises. The last part of the session concentrates on finding a good activity-rest balance after the surgery. Patients are encouraged to engage in pleasant or valued activities. After session 2, patients are asked to continue the relaxation exercises, write down their thoughts about cancer, pain, and other complaints in the thoughts diary, and document their pleasant and valued activities.

Session 3 starts with getting insight in one’s own coping strategies. The education part focuses on cognitive restructuring. Patients receive exercises to change their unhelpful (catastrophizing) thoughts into more helpful thoughts. After session 3, patients continue the homework assignments, complemented by the cognitive restructuring part in the thoughts diary.

Sessions 4 is devoted to coping strategies and valued activities. The role of avoidance in the persistence of complaints is discussed. It is explained how valued activities can counterbalance difficult and stressful situations. Therefore, patients are asked to think about things that are genuinely important to them during this period. Using the acronym SMART (Specific-Meaningful-Acceptable-Realistic-Time framed), they describe activities that give them energy and help them endure the difficult treatment. Homework assignments are continued.

Session 5 is devoted to rehearsal, continued practice, and maintenance. After a recap of the first four sessions, patients are guided into the construction of their own action plan. They write down how to recognize their own alarm signals and which of the exercises and techniques from the intervention are most helpful to them.

The intervention is hosted on a specialized eHealth platform (Karify®, Utrecht, Netherlands), which allows secured communication with a therapist.

#### AMAZONE active control intervention (EDU)

The active control intervention (EDU) consists of five sessions that present information that is taken from publicly available sources. It has the same outline as the e-CBT intervention: one online session pre-operatively and four post-operatively and three appointments with a therapist to monitor the intervention, increase motivation, and address possible questions concerning the intervention. The control intervention is hosted on Qualtrics (Qualtrics, Provo, Utah, USA).

Session 1 gives information about the different types of surgery and pain treatment. Patients receive tips on how to prepare for surgery and handle possible complaints the days after surgery. This comprises a series of physical exercises that are recommended after breast cancer surgery. For the patients who want to gain additional information, a list of reliable sources is presented.

Session 2 is devoted to good communication about the disease and treatment.

Session 3 gives information about fatigue during cancer treatment. Different causes are discussed as well as tips on how to cope with fatigue.

Session 4 focuses on a healthy weight and food pattern. Patients can choose the topic(s) they want to read more about: unwanted weight gain, diminished appetite, changed taste, and information on food and medication.

Session 5 consists mainly of rehearsal of the main points of previous sessions.

### Criteria for discontinuing or modifying allocated interventions {11b}

Subjects can leave the study at any time for any reason if they wish to do so without any consequences. The responsible physician or the investigator can decide to withdraw a subject from the study for urgent medical reasons.

### Strategies to improve adherence to interventions {11c}

After enrollment and before the first online session, the randomized patients have an online appointment (via secured platform) to explain the aim of the program and address concerns. Also, after sessions two and five, patients have appointments with their therapists to discuss questions regarding the online sessions and motivate them. This appointment is also meant to create therapeutic alliance and protocol adherence.

When patients forget to fill in the online questionnaires or open the online sessions, they receive reminders via mail or SMS. Patients can also contact the research team if needed.

### Relevant concomitant care permitted or prohibited during the trial {11d}

AMAZONE does not interfere with the planned oncological treatment nor prohibits any other necessary medical, psychological, or psychiatric treatment. In case additional psychological or psychiatric treatment is initiated during the 2 months after surgery in the randomized groups, a sensitivity analysis will be applied to assess potential confounding by this subgroup.

### Provisions for post-trial care {30}

The AMAZONE trial is qualified as a low risk study. Harm from e-CBT or EDU is not expected.

### Outcomes {12}

#### Main study parameter/endpoint

The main outcome of the study is the prevalence of significant PPBCT in the operated area at six months, defined as a score ≥ 3 on an 11-point numeric rating scale (NRS).

#### Secondary study parameters/endpoints

Secondary outcomes of the study are pain intensity scores (intercept and slope) during the first postoperative week (NRS, pain diary), cessation of postoperative opioid use (no. of days), and PPBCT prevalence after 12 months. Mean PPBCT intensity in the operated area (NRS), presence of neuropathic pain (Doleur neuropathique (DN4)) [59], and pain interference (Brief Pain Inventory (BPI) [60], measured at 2, 6, and 12 months.

(Pain) sensitivity is assessed with quantitative sensory testing (QST) before and at 6 months post-surgery. QST is measured at the bilateral pre-axillary dermatomes Th 3. In patients with persistent postoperative pain in the operated area, the 6-month QST measurement is performed in the painful and the corresponding contralateral location. QST measurements are performed according to the protocol developed by the DFNS [61]. Conditioned pain modulation (CPM) is measured before, at 1 week postoperatively and 6 months later according to the suggestions of Yarnitsky et al. [62]. The chosen CPM algorithm compares three repetitions of pressure pain threshold measurements in the thenar contralateral to the operated side, before and immediately after a cold pressor test delivered to the other hand with ice water.

In addition the psychological parameters anxiety, fear of recurrence, catastrophizing, and depression are assessed together with the cancer related quality of life before and up until 12 months after surgery.

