#### Secondary study parameter(s)

The mean daily postoperative pain scores over the 1-week period will be compared between the groups using linear mixed-effects regression with a random intercept and slope to account for multiple measurements over time within patients. Covariance between random effects will be estimated using an unstructured covariance matrix. Correlation between measurements over time will be modeled using a first order autoregressive structure. Both differences in average pain level over time and differences in trend across time will be assessed.

Time to opioid cessation will be analyzed with the Kaplan-Meier method and compared using the log-rank test.

Mean pain intensity and pain interference at 2, 6, and 12 months will be compared using linear mixed-effects regression with regards to group differences and time course.

Quality of life at 6 and 12 months will be compared between groups using the independent-samples *t*-test.

The effect of surgery on QST and CPM parameters will be analyzed by paired-sample *t*-test on the pre-surgical and 1-week and 6-months post-surgical results. The intervention effect on QST and CPM will be assessed with linear mixed-effects regression at the three time points.

Intervention effects on pain catastrophizing, anxiety, depression and fear of cancer recurrence at two months will be evaluated using the independent-samples *t*-test. With linear mixed-effects, regression differences in level and slope are compared between e-CBT and EDU taking all longitudinal measurements into account.

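### At 6 months the QST site follows the pain in patients with persistent pain, while the planned pre-post and e-CBT versus EDU comparisons make no provision for a change of site

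*Protocol article*

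**What the plan says.** Under Outcomes {12}, Secondary study parameters/endpoints, the protocol article gives the standard site: "QST is measured at the bilateral pre-axillary dermatomes Th 3". QST is done before surgery and at 6 months. The same paragraph then makes an exception: "In patients with persistent postoperative pain in the operated area, the 6-month QST measurement is performed in the painful and the corresponding contralateral location". It does not say that Th3 is tested as well in these patients. It describes no baseline test at the location that later becomes painful, and that location cannot be known before surgery.

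The primary endpoint is the "prevalence of significant PPBCT in the operated area at six months, defined as a score ≥ 3 on an 11-point numeric rating scale". The QST exception uses nearly the same condition, but without the NRS threshold.

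Under Statistical methods, Secondary study parameter(s), the analysis has two parts. First, "The effect of surgery on QST and CPM parameters will be analyzed by paired-sample" t-tests "on the pre-surgical and 1-week and 6-months post-surgical results". Second, "The intervention effect on QST and CPM will be assessed with linear mixed-effects regression at the three time points". Neither part contains a term, stratum or exclusion for test site. The section on the choice of comparators {6b} also gives the TAU cohort a role here: "This group serves as reference group for the primary outcome PPCBT and for the QST/CPM measurements".

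**The concern.** A pre-post comparison of a local sensory measure needs the same place at both visits. Here every patient has Th3 at baseline. At 6 months, patients without persistent pain have Th3 again and patients with it have the painful spot. In the second group the paired difference combines any change in sensitivity with the difference between two places on the body. Part of that difference may be genuine sensitisation at the painful spot, but without a baseline there it cannot be separated from ordinary variation between sites.

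The choice of site is also made after randomisation, by a state that e-CBT is meant to change. If the arms differ in pain prevalence, they differ in the mix of sites tested. An arm difference in QST could then appear with no effect on processing at a fixed site, or a real effect could be masked. At stake is the QST part of the mechanistic objective: nociceptive signal transmission, the effect of surgery on it, and the exploratory comparison with TAU.

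**Working it through.** **Inputs from the protocol article, Sample size {14}.** Expected 6-month prevalence is 50% in EDU and 25% in e-CBT; 55 per group; 80% power; alpha 0.05; 20% drop-out; 138 in total.

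**The plan's own figure.** With two-sided alpha (an assumption; sidedness is not stated) and the unpooled normal formula:

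n = (1.960 + 0.842)² x (0.50 x 0.50 + 0.25 x 0.75) / 0.25² = 7.85 x 0.4375 / 0.0625 = 54.9, so 55 per group.

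55 / 0.80 = 68.75, so 69 per arm and 138 in total. The sample size reproduces and is not in dispute. The prevalences are used here only to estimate how many patients fall under the changed site rule.

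**Assumption.** Let d be the mean difference, in SD units, between the QST value at the painful site and the value Th3 would have given in the same patient at the same visit. The documents do not give d; the range taken is 0 to 1 SD.

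**Size of the distortion** with no true change at Th3, if every painful spot lies outside Th3:

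- Pre-post, arms pooled: (0.50 + 0.25)/2 x d = 0.375 x d, or 0 to 0.38 SD.
- Between arms: (0.50 − 0.25) x d = 0.25 x d, or 0 to 0.25 SD.
- Equal pain rates of 37.5% in both arms: the pre-post term stays at 0.375 x d and the mean between-arm term is 0.

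**Effect on the tests.** This was simulated with 55 per arm, baseline to 6-month correlation 0.5 (assumed), no true change and 10,000 runs. A paired t-test was run on the pooled arms and a two-sample t-test on change scores. Rejections at the 5% level:

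| d (SD) | Pre-post shift (SD) | Pre-post rejected | Between-arm shift (SD) | Between-arm rejected |
|---|---|---|---|---|
| 0 | 0 | 4.8% | 0 | 5.1% |
| 0.3 | 0.11 | 21% | 0.08 | 7% |
| 0.5 | 0.19 | 48% | 0.13 | 10% |
| 0.8 | 0.30 | 83% | 0.20 | 17% |
| 1.0 | 0.38 | 95% | 0.25 | 21% |

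With 37.5% in both arms, between-arm rejection stays at about 5% for every d, while pre-post rejection is essentially as in the table. A fixed site corresponds to the row d = 0.

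**TAU.** The sample size section expects 30% prevalence overall and 30% of patients screening positive. With 50% prevalence in those, the implied prevalence in TAU is (0.30 − 0.30 x 0.50)/0.70 = 21%. EDU and TAU would then also differ in site mix, at about 50% against 21%.

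**The case against.** The strongest reply is that replacement of Th3 is inferred. The article never says in so many words that Th3 is dropped. It condenses a fuller protocol, refers QST to a published standard protocol, and may leave the handling of site to an analysis plan. Testing the painful area and its mirror side is also a sound way to characterise persistent pain. This stands as a reason to ask for clarification before concluding that Th3 values are absent. It does not remove the point: the sentence describes the 6-month measurement itself, not an additional one, and no analysis plan can recover Th3 values that were never taken. The mirror site supports a side-to-side comparison at 6 months, but the article plans none, and it does not repair the pairing with baseline.

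Some patients will have pain at Th3 and do not change site. A reader might take 50% and 25% as the shares that switch. The documents do not support that: the figures count pain at NRS 3 or more wherever it lies in the operated area, so they overcount where it lies at Th3. The trigger for the site change carries no NRS threshold, which could push the share the other way.

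A reader might also infer that the bias favours e-CBT. The documents do not say how a painful site differs from Th3 or which direction of QST is favourable. The background names both nerve damage and central sensitisation, which could move parameters in opposite directions.

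Finally, a reader might conclude that the mechanistic objective cannot be answered. That goes too far. CPM is measured at the thenar in everyone and addresses central pain inhibition, and QST is unaffected in patients tested at Th3 on both occasions.

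**Conclusion.** The point holds for QST. As written, the 6-month site depends on a post-randomisation state close to the primary outcome, and the planned analyses make no allowance for it. The pre-post comparison is exposed whatever the treatment effect. The between-arm comparison is exposed only if pain rates differ, and less strongly: at d = 1 SD, 21% false rejection against 95% pre-post.

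The sizes rest on the design prevalences, on every painful spot lying outside Th3, and on an assumed d. The rejection rates also rest on the assumed correlation and on QST in all 55 patients per arm. The section on outcome collection {18a} speaks of the centres that assess QST and CPM, so fewer may be measured. The sign of the distortion is not known. The primary endpoint and CPM are untouched, so this should be corrected but does not threaten the main result.

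**What to change.** In Secondary study parameters/endpoints, state that bilateral Th3 is re-tested at 6 months in every QST patient, and that painful-site and mirror-site QST is an additional measure in patients with pain. In the statistical section, state that the pre-post, e-CBT versus EDU and TAU comparisons use Th3 only. Report painful-site data descriptively or as a 6-month side-to-side comparison. If Th3 is already re-tested in practice, a clarifying sentence in the outcomes section and the named analysis site in the statistical section are enough.

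The cost is extra test time at the 6-month visit for patients with pain, and an amendment communicated to sites and ethics committees.

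Recruitment began in June 2021, so some patients may already have been tested only at a painful site outside Th3. Do not pair that value with baseline Th3. Report the number of such patients by arm, and acknowledge that their missing Th3 values depend on the outcome. The default imputation in {20c} does not solve this: predictive mean matching could draw donors only from patients who were tested at Th3, that is, those without persistent pain or with pain at Th3. Use a sensitivity analysis over a stated range of Th3 values for these patients instead of relying on it.
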